## Abstract

**Background:**

Inflammatory bowel disease (IBD) is a chronic condition of the bowel that affects over 1 million people in the United States. The recurring nature of disease makes IBD patients ideal candidates for patient-engaged care that is centered on enhanced self-management and improved doctor-patient communication. In IBD, optimal approaches to management vary for patients with different phenotypes and extent of disease and past surgical history. Hence, a single quality metric cannot define a heterogeneous disease such as IBD, unlike hypertension and diabetes. A more comprehensive assessment may be provided by complementing traditional quality metrics with measures of the patient’s quality of life (QOL) through an application like HealthPROMISE.

**Objective:**

The objective of this pragmatic randomized controlled trial is to determine the impact of the HealthPROMISE app in improving outcomes (quality of care [QOC], QOL, patient adherence, disease control, and resource utilization) as compared to a patient education app. Our hypothesis is that a patient-centric self-monitoring and collaborative decision support platform will lead to sustainable improvement in overall QOL for IBD patients.

**Methods:**

Participants will be recruited during face-to-face visits and randomized to either an interventional (ie, HealthPROMISE) or control (ie, education app). Patients in the HealthPROMISE arm will be able to update their information and receive disease summary, quality metrics, and a graph showing the trend of QOL (SIBDQ) scores and resource utilization over time. Providers will use the data for collaborative decision making and quality improvement interventions at the point of care. Patients in the control arm will enter data at baseline, during office visits, and at the end of the study but will not receive any decision support (trend of QOL, alert, or dashboard views).

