## Methods

### Study Design

This is a phase III, single-center, pragmatic randomized controlled trial (RCT) to evaluate if a patient-centric self-monitoring and collaborative decision support platform will lead to sustainable improvement in overall QOL for IBD patients. It is intended that 300 patients with IBD will be recruited into the study (allocation ratio 1:1; Figure 4). After meeting all the inclusion criteria with no exclusions, patient is asked to complete a tablet-based screening questionnaire at the end of which patient is randomized at the point of care to intervention or control arm. Patients in the control arm will receive an IBD education app PIN whereas the intervention arm will receive HealthPROMISE app PIN (Figure 3). Intervention patients enter their data once every 2 weeks and this data is then made visible to providers using a Web-based dashboard integrated with the EHR (Figures 4 and 5). Intervention and control apps will be provided free of charge to patients, and patients will be given $25 after completing initial and end of study questionnaires.

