### Study Population

Patients will be recruited at outpatient and inpatient facilities in an academic center through informational paper and electronic flyers. Once enrolled, patients will receive a walkthrough of the app, which includes access to a training video. The provider dashboard will also have access to the training video. Eligible patients will be 18 years or older, have a mobile phone or access to the Internet at home, and be able to complete a Web-based questionnaire in English. Exclusion criteria include the inability to communicate with the investigators and comply with the study requirements, presence of short bowel syndrome or stoma, and presence of a condition or disease that, in the opinion of the investigators, may make it difficult for the patient to use the HealthPROMISE app, including, but not limited to, advanced dementia.

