### Statistical Analysis Plan

#### Overview

We will use SAS 9.2 (SAS Institute, Inc) to calculate frequencies and percentages for categorical factors and means with standard deviations and/or percentiles for continuous factors. Pearson’s chi-square tests will be used for primary outcome (number of quality indicators met in HealthPROMISE vs control arm) and secondary outcomes. We will calculate percentage score for each patient at baseline and at week 104 ([number of quality metrics met/quality metrics eligible]*100). Change in the percentage score from baseline to week 104 will be aggregated for each arm to calculate percentage-point improvement in quality metric, similar to the strategy by Cebul et al [26].

Analysis of covariance (ANCOVA) will be performed to assess differences in the area under the curve of QOL scores while adjusting for baseline QOL score. To assess the association between patient and practice characteristics and achievement of eligible quality metrics, we will use multivariable analyses. Since the data will be hierarchically structured, with patients clustered within physicians and metrics clustered within patients, we will construct multilevel, generalized, linear mixed models with random effects to determine predictors of quality care, similar to the strategy used by Kanwal et al [27]. Independent variables will include demographic characteristics (age, gender), education and income level, race and ethnicity, computer usage, eHealth literacy scores, clinical characteristics (comorbidities, phenotype, disease severity), and provider characteristics (gender, age, site of practice, years of practice, presence of nurse practitioner).

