### Conclusion

HealthPROMISE is a unique cloud-based PRO and decision support tool that empowers both patients and providers. Patients track their QOL and symptoms, and providers can use the visual data in real time (integrated with EHRs) to provide better care to their entire patient population. Using pragmatic trial design, we hope to show that IBD patients who participate in their own care and share in decision making have appreciably improved outcomes when compared to patients who do not [28,29].

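### Shared providers and provider-level quality reports allow some spillover into the control arm, and the primary chi-square test ignores provider

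*Protocol article*

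**What the plan says.** **Unit of allocation.** Methods, Study Design describes a single-center trial with 1:1 allocation in which the "patient is randomized at the point of care to intervention or control arm".

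**Providers.** Table 1 sets a goal of 10 trained providers and 300 enrolled patients. Study Population adds: "The provider dashboard will also have access to the training video". No section assigns providers to an arm.

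**Provider side of the intervention.** Abstract, Methods: "Providers will use the data for collaborative decision making and quality improvement interventions at the point of care". Study Design says that intervention patients' fortnightly entries are shown to providers on a dashboard integrated with the health record.

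**What controls do not get.** The same Abstract section says that control patients "will not receive any decision support (trend of QOL, alert, or dashboard views".

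**Reports.** The outcome rows of Table 1 list improvement in quality-of-care metrics, with provider and center as the target group and quarterly reports. No restriction by arm is given.

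**Endpoint and test.** The primary endpoint is quality indicators met, compared by Pearson's chi-square (Statistical Analysis Plan, Overview). That section also describes the data as hierarchical, "with patients clustered within physicians and metrics clustered within patients", but uses mixed models only to find predictors of quality care.

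**Sample size.** Sample Size Justification assumes 85% in the intervention arm, at least 15% lower in the control arm, and 95 per arm for 80% power at a one-sided 5% level. It allows 30% attrition and recruits 300.

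**The concern.** When part of an intervention works through clinicians, and those clinicians treat both arms, a practice prompted for an intervention patient can carry over to a control patient. The endpoint here is sensitive to that, because quality indicators reflect at least in part what the provider orders, checks or records. Quality reports fed back to providers and the center are a second route, since nothing limits them to intervention patients.

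Spillover of this kind would move the control rate toward the intervention rate. It does not raise the type I error. It understates the effect and costs power, so a null result would be harder to interpret.

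The second issue is separate. If the endpoint varies by provider, a chi-square that ignores provider leaves chance differences in provider mix between arms unadjusted and gives up precision. This is random error, not bias.

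**Working it through.** **1. Are providers shared?** 300 patients / 10 providers = about 30 patients per provider. With 1:1 allocation of individual patients at the point of care, that is about 15 per arm for each provider on average. The article does not state that a provider sees both arms, but under this design it is hard to avoid.

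**2. Reproduce the plan's sample size.** Inputs from Sample Size Justification: p1 = 0.85, p2 = 0.85 − 0.15 = 0.70, one-sided alpha 5% (z = 1.645), power 80% (z = 0.8416). The mean proportion is pbar = 0.775. The pooled-variance formula without continuity correction is

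n = [1.645·√(2·pbar·(1 − pbar)) + 0.8416·√(p1(1 − p1) + p2(1 − p2))]² / (p1 − p2)²

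= [1.645·√0.34875 + 0.8416·√0.3375]² / 0.0225 = 94.8, rounded up to 95.

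This matches the stated 95 per arm. Power at 95 per arm is 80.1%.

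**3. Evaluable number.** 300 recruited gives 150 per arm, and 150 × 0.70 = 105 per arm after 30% attrition.

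**4. Power under spillover.** Let c be the share of the 15-point effect that reaches controls. The article gives no value for c, so the values below are assumptions. The intervention rate stays at 0.85 and the control rate becomes p2 = 0.70 + 0.15c. Then

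power = Φ{ [(p1 − p2)·√n − 1.645·√(2·pbar·(1 − pbar))] / √(p1(1 − p1) + p2(1 − p2)) }.

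Example with c = 0.20 and n = 105: p2 = 0.73, pbar = 0.79, and (0.12·√105 − 1.645·√0.3318) / √0.3246 = 0.495, so power = 69.0%.

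| Share of effect reaching controls | Control rate | Difference (points) | Power, 105 per arm |
|---|---|---|---|
| 0 | 70% | 15 | 83.5% |
| 10% | 71.5% | 13.5 | 76.9% |
| 20% | 73% | 12 | 69.0% |
| one third | 75% | 10 | 56.7% |
| half | 77.5% | 7.5 | 40.0% |

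Sample Size Justification also names a two-tailed test. On that basis, power at 105 per arm is 74.3% with no spillover and 57.0% at 20%.

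**5. Where provider enters the analysis.** The Overview assigns Pearson's chi-square to the primary outcome and mixed models with random effects to the predictor question. The provider structure is therefore recognised but not carried into the comparison of arms.

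**The case against.** The strongest reply is that the plan already separates the arms. Controls get no trend, alert or dashboard view, and Study Design ties the dashboard to data entered by intervention patients. Read plainly, a provider has no dashboard view of a control patient. This stands, and it removes the most direct route.

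A reader might infer that controls receive part of the intervention and that the difference is diluted. The article does not establish this. Spillover is an inference, and no passage gives its size. The training described is an app video, with nothing to say that it teaches the indicators. The indicators come from national societies and a provider Delphi panel, so they are not knowledge that only the app releases. The indicator list is not shown, and providers or patients may update it, so the endpoint cannot be called purely provider behaviour.

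A reader might also take "to provide better care to their entire patient population" to mean that the dashboard is used for controls during the trial. The phrase occurs in the Abstract Conclusions, the Objectives and the closing Conclusion, where it describes the product. It is not a trial procedure.

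Nor can one say that the 15-point difference ignores spillover. The plan expects a gap of at least 15% and does not say whether that is net of spillover. Whether randomisation is stratified by provider is likewise not stated, and a condensed article may leave this to the full protocol.

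What survives is narrower: nothing limits provider learning or the provider and center reports by arm, and the stated primary test omits provider.

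**Conclusion.** The point holds as a design improvement, not as a demonstrated bias. Individual randomisation among a small group of very probably shared providers, with an endpoint that depends at least partly on them and quality reports not limited by arm, makes some spillover toward no difference possible. Its size is unknown. With 105 evaluable per arm and one-sided 5%, the plan starts at 83.5% power, and an assumed 10% spillover is enough to bring it below 80%. The values for one third and half (56.7% and 40.0%) show sensitivity and are not predictions.

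The figures rest on the 85% and 70% rates, on 30% attrition, and on the all-indicators-met version of the endpoint used in the sample size calculation. The stated primary endpoint is the number of indicators met, so its power may differ.

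Independently of spillover, the primary chi-square ignores a clustering that the plan itself recognises. A reader might infer that the sample size therefore needs a cluster-trial design effect. It does not follow, because patients rather than providers are randomised. The cost is precision and unadjusted chance imbalance in provider mix.

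**What to change.** Keep individual randomisation, and make these changes:

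1. Replace the plain chi-square for the primary outcome with a comparison stratified by, or adjusted for, treating provider. Use provider as a stratum in the tablet randomisation if it is not one already. This deals with provider imbalance and precision. It does not reduce spillover.
2. Until follow-up ends, limit quality-metric reports and metric-driven quality improvement by providers to intervention-arm patients, or withhold the provider and center quality reports. Learned habits may still carry over.
3. Report the control arm's own change in percentage score from baseline as a check for spillover. The Overview already plans this change for each arm. A rise in controls would be compatible with spillover but would not prove it, since usual care may also improve over time.

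The cost is a change to the analysis text, possibly one stratification factor, and a restriction on reporting. The real downside is that wider quality feedback at the center is delayed until the trial ends.

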**Results:**

Enrollment in the trial will be starting in first quarter of 2015. It is intended that up to 300 patients with IBD will be recruited into the study (with 1:1 allocation ratio). The primary endpoint is number of quality indicators met in HealthPROMISE versus control arm. Secondary endpoints include decrease in number of emergency visits due to IBD, decrease in number of hospitalization due to IBD, change in generic QOL score from baseline, proportion of patients in each group who meet all eligible outpatient quality metrics, and proportion of patients in disease control in each group. In addition, we plan to conduct protocol analysis of intervention patients with adequate HealthPROMISE utilization (more than 6 log-ins with data entry from week 0 through week 52) achieving above mentioned primary and secondary endpoints.

**Conclusions:**

HealthPROMISE is a unique cloud-based patient-reported outcome (PRO) and decision support tool that empowers both patients and providers. Patients track their QOL and symptoms, and providers can use the visual data in real time (integrated with electronic health records [EHRs]) to provide better care to their entire patient population. Using pragmatic trial design, we hope to show that IBD patients who participate in their own care and share in decision making have appreciably improved outcomes when compared to patients who do not.

**Trial Registration:**

ClinicalTrials.gov NCT02322307; https://clinicaltrials.gov/ct2/show/NCT02322307 (Archived by WebCite at http://www.webcitation.org/6W8PoYThr).

## Introduction

### Background

Inflammatory bowel disease (IBD) is a chronic condition of the bowel that affects over 1 million people in the United States [1]. Although the incidence of IBD is rising, the precise cause of the disease remains unknown. Medical treatment for IBD has improved significantly in recent years; however, current efforts are largely ameliorative rather than curative. As a result, IBD patients have to cope with a lifelong condition in which there are commonly remissions and relapses. This makes IBD patients the ideal candidates to target for improved self-management when it comes to care.

While diseases such as hypertension and diabetes render themselves well to quality improvement efforts because of standardized indicators such as blood pressure and hemoglobin A1C respectively, a single quality-of-care (QOC) metric cannot define a heterogeneous disease such as IBD, where optimal approaches to manage patients differ between different phenotypes. Furthermore, IBD profoundly affects patients not only physically but also in social, professional, and emotional activities [1,2]. Overall well-being of IBD patients cannot be achieved if these dimensions are not improved [3-6]. Unfortunately, most of the currently proposed quality improvement initiatives in IBD are process measures and do not include quality of life (QOL) or clinically meaningful outcomes such as clinical remission or hospitalizations that matter most to patients and their state of health [7].

Chronic diseases affect almost 1 out of every 2 Americans and produce a significant burden on US health care [8,9]. Meaningful health system quality improvement warrants patient-provider interaction focused on QOC and QOL in chronic diseases like IBD [10,11]. For health care teams, the question remains: how do we better engage patients without placing increased time constraints on health care staff? Based on pilot work, we believe that patients are as eager as physicians, if not more, to improve their QOL and care, and involving them as partners to improve care can bring remarkable efficiency to current quality improvement efforts [3].

### Objectives

HealthPROMISE [12] is a unique cloud-based PRO (patient-reported outcome) and decision support platform developed at Sinai AppLab, Icahn School of Medicine at Mount Sinai [13] Patients track their QOL and symptoms, and providers can use the visual data in real time (integrated with electronic health records [EHRs]) to provide better care to their entire patient population (Figures 1 and 2). HealthPROMISE addresses unique challenges to improving quality and outcomes for patients with a chronic disease like IBD.

**Figure 1 figure1:**
[figure not shown]
Quality of life measure.

**Figure 2 figure2:**
[figure not shown]
Short Inflammatory Bowel Disease Questionnaire.

### Adopting a Broader Definition of Quality

A more comprehensive assessment may be provided by complementing the QOL with quality of care metrics (Figure 3). QOL has been defined as “a global measure of patient’s perceptions, illness experience, and functional status that incorporates social, cultural, psychological, and disease-related factors” [14]. QOL metrics can be used to inform outcomes in clinical encounters, monitor population health, and as end points in clinical trials [14]. National Institutes of Health (NIH) Patient Reported Outcomes Measurement Information System [15] and more recently Project Health Design [16] have provided valuable insights into generic measurements for QOL. To address this challenge, we have previously defined a set of comprehensive quality indicators for IBD patients through analyzing different focus groups to study what factors patients assess and value when defining “quality” in terms of living with IBD and the treatment of IBD. Additionally, through semi-structured interviews and Delphi panel sessions with 15 providers, provider input on QOC was recorded.

**Figure 3 figure3:**
[figure not shown]
Quality of care.

### Decreasing the Burden of Measuring Quality

Quality improvement efforts so far have shown that measuring even limited QOC metrics carries a prohibitively high administrative and cost burden. The estimated costs from the Institute for Healthcare Improvement quality improvement initiative for either congestive heart failure or diabetes ranged from $81,000 to $148,000 per organization [17]. Chen and Bates have shown that total reported costs for inpatient quality improvement for a hospital ranged from $2 million to $21 million, with the majority of costs attributed to collecting and reporting quality metrics for national organizations [18]. This burden of measuring quality is likely to increase exponentially when multiple QOC metrics are included in quality measurement. To address this challenge, patient- and physician-provided indicators were incorporated into a mobile health strategy platform, HealthPROMISE, that allows patients to record and self-report their QOL and treatment with regards to their IBD.

### Improving the Effectiveness of Quality Improvement Initiatives

Currently, there is no well-accepted national model for quality improvement. Most of the quality improvement projects to date involve some kind of data abstraction from the clinical encounters that is fed into a registry to allow benchmarking, risk adjustment, and quality reporting. This cycle takes anywhere from a few weeks to a few months and happens long after the patient has left the health care facility. Patients are not involved in measuring or improving quality. Thus, an important patient-physician “productive interaction” opportunity to improve outcomes at the point of care is missed [19]. In HealthPROMISE, patients track symptoms and QOL before office visits and in waiting rooms, thus allowing meaningful discussion about QOC to take place during office visits (Figures 1 and 2).

The aim of this research protocol is to evaluate the patient-centric Web- and mobile-based application, HealthPROMISE, where IBD patients longitudinally measure their QOC and QOL metrics and physicians use this information for collaborative decision making and improving patient outcomes. Our hypothesis is that a patient-centric self-monitoring and collaborative decision support platform will lead to sustainable improvement in overall QOL for IBD patients.

## Methods

### Study Design

This is a phase III, single-center, pragmatic randomized controlled trial (RCT) to evaluate if a patient-centric self-monitoring and collaborative decision support platform will lead to sustainable improvement in overall QOL for IBD patients. It is intended that 300 patients with IBD will be recruited into the study (allocation ratio 1:1; Figure 4). After meeting all the inclusion criteria with no exclusions, patient is asked to complete a tablet-based screening questionnaire at the end of which patient is randomized at the point of care to intervention or control arm. Patients in the control arm will receive an IBD education app PIN whereas the intervention arm will receive HealthPROMISE app PIN (Figure 3). Intervention patients enter their data once every 2 weeks and this data is then made visible to providers using a Web-based dashboard integrated with the EHR (Figures 4 and 5). Intervention and control apps will be provided free of charge to patients, and patients will be given $25 after completing initial and end of study questionnaires.

